### Phase 1 Procedures

The purpose of Phase 1 is to adapt the CBT manual to be suitable for CBT group treatment in DUI programs and receive feedback from DUI program clients to determine if it is appropriate and helpful.

#### CBT conceptual framework

CBT extends cognitive therapy through use of behavioral techniques [61]. Cognitive therapy is based on a model that suggests that “distorted or dysfunctional thinking (which influences the patient’s mood and behavior) is common to all psychological disturbance” [62]. This cognitive model is common across treatments for depression and substance use. The model posits that substance abuse is perpetuated by maladaptive thoughts and beliefs [63]. Core techniques of CBT, such as emotional regulation and positive reframing, have been adapted to be culturally meaningful for Latinos (e.g., use of imagery involving light, which is analogous to Christian imagery embraced by some Latinos; reference to social/peer/family pressure, familism, and fatalism) and have been found to improve retention and treatment outcomes in Latino populations [46, 64, 65].

The central tenets of the CBT treatment are based on improving coping skills [32]. Lack of coping skills can increase the likelihood of drinking when confronted with high-risk scenarios such as feeling stressed or attending a social gathering where alcohol is served [66–68]; thus, the primary goal of the CBT treatment is to reduce negative consequences that arise from drinking behavior and drinking and driving by increasing awareness of potential high-risk situations through the use of coping skills.

#### CBT group treatment adaptation

In Phase 1, we will follow adaptation procedures from our previous research [53, 69, 70] to ensure that the CBT treatment is relevant for diverse DUI clients and feasible to administer within the group DUI setting. We will follow Barrera and Castro’s [71] framework, which includes information gathering from key informants (i.e., DUI clients, counsellors, administrators), preliminary adaptation of the CBT manual, pilot testing using focus groups with DUI clients, and further revisions incorporating client feedback from the focus groups. Our goal is to ensure that the CBT treatment is compatible for clients who have different cultural patterns, meanings, and values [72], and that we maintain fidelity to the core elements of CBT. We will gather information by conducting approximately ten focus groups with DUI clients. These focus groups will consist of 8–10 existing clients recruited from DUI usual care groups currently in session. We will first conduct one to two focus groups prior to adapting the CBT manual to obtain general reactions about the CBT model, potential session topics, and important cultural or other adaptations we need to account for when adapting the CBT treatment (e.g., language describing drinking and drinking and driving). During the focus groups, we will demonstrate parts of the CBT sessions and then ask clients for their feedback. Their feedback will be elicited in two main sections: (1) Acceptability and feasibility of the CBT group material (e.g., “Which messages were the most convincing to reduce drinking while driving? Least convincing? What was the most helpful information that you saw? Least helpful? What do you think would help other clients?”); and, (2) Cultural acceptability of the treatment content (e.g., “How can we make the program helpful to people from different backgrounds? What messages, images, or phrases are most meaningful, within and across cultures?”). We will iteratively make changes to our treatment manual following each focus group. Our final step in the treatment adaptation process will be to revise our manual to incorporate suggestions commonly brought up across the focus groups.

#### Focus group recruitment

Recruitment for the focus groups will use effective strategies from our previous research [19, 53], and the targeted recruitment of English speakers is consistent with the population that attends LA County DUI programs. We will be recruiting clients already enrolled in DUI Usual Care because we want feedback about how their experiences in Usual Care compares with the CBT group information we are presenting; we also want opinions from a variety of clients at different phases in the program (e.g., just started program, about to end program) who can provide insight on what information is helpful or unhelpful in reducing risk of DUI recidivism. DUI counsellors will briefly describe the study and pass out consent-to-contact forms. Clients will be asked to return their form in an envelope (whether blank or completed) to avoid feelings of coercion to participate. Envelopes will be given to their counsellor who will return them to research staff. Research staff will call clients who consent to be contacted, to schedule an in-person appointment to obtain informed consent for study participation.

### Phase 1 analysis plan

Focus groups will be audio recorded. Collection and interpretation of focus group data will follow approaches we have used in previous work [53, 73, 74]. Following grounded theory analyses [75], we will discuss each category and generate underlying themes. Classic content analysis will be used to identify quotes that fit each theme [76, 77]. Then, we will sort quotes by theme and reach a consensus on any discrepancies. This analysis will allow us to understand feasibility and acceptability, and will inform the delivery of CBT in a diverse DUI setting.

### Phase 2 procedures

The purpose of Phase 2 is to determine the efficacy of a 9-session CBT group treatment for AUD compared to UC among individuals who are court-ordered to attend a 3-month DUI program for a first-time conviction. We will also examine predictors of CBT efficacy to further understand the characteristics of participants who benefit most from treatment.

Participants (N = 300) will be recruited at intake (see Fig. 1). Upon enrolling in the DUI program, program staff will ask clients if research staff can contact them about a research study. Interested clients will complete a consent-to-contact form. After DUI program staff has completed their procedures, on-site research staff will screen, obtain consents, and randomize potential clients. For rare instances when staff is unavailable, DUI staff will fax consent-to-contact forms to a secure fax machine and research staff will screen and gain consent from the client by phone. Staff will screen for at-risk drinking using the AUDIT-C [four or more (if male) or three or more (if female or other)] [50]. Participants will be asked to complete a baseline survey, post-treatment survey at DUI program completion (i.e., 3-months post-baseline), and a follow-up survey 6 months after program completion. Participants will receive a $25 gift card for the baseline survey, $25 for the post-survey, and $50 for the 6-month follow-up. All participants will be followed, regardless of whether they complete UC or CBT, and we will conduct intent to treat analyses.

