### Specific aims and hypotheses

The specific aims of this project are to: (1) evaluate the efficacy of CBT on reported heavy drinking, percent days abstinent, alcohol-related self-efficacy, and intent to drink and drive; and, (2) evaluate factors associated with improved treatment outcomes and 2-year DUI recidivism by examining whether race/ethnicity, gender, acculturation, and alcohol situational norms predict treatment outcomes and DUI recidivism. We hypothesize that those randomized to CBT will have greater improvements in alcohol-related outcomes at 6-month follow-up and lower likelihood of recidivism two years later than those in UC.

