## Methods/design

### Overview of study procedures

All procedures have been approved by the Institution’s Review Board. There are two phases to the study. The first phase will be focused on adapting the CBT treatment for the DUI population by eliciting feedback about each session from focus group participants. The second phase will be a randomized trial of the adapted 9-session CBT treatment compared to Usual Care. Potential participants will be screened for at-risk drinking using the AUDIT-C [four or more (if male) or three or more (if female or other)] [50], randomized to either UC or CBT, and then asked to complete self-administered assessments at baseline, immediately post-treatment (i.e., 3-months post-baseline), and 6-months post-treatment. We will also assess recidivism up to 48 months after the treatment ends using administrative data collected by the State of California. Analyses will be conducted to compare overall group efficacy between CBT and UC. We will also analyze predictors of treatment response and recidivism by examining whether race/ethnicity, gender, acculturation, and alcohol situational norms predict treatment outcomes and DUI recidivism.

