### Phase 3 Procedures

In Phase 3, we will explore whether gender, race/ethnicity, acculturation, and alcohol situational norms are predictors of our primary treatment outcomes (rates of heavy drinking, and percent days abstinent) and DUI recidivism (alcohol-related violations). Such analyses will allow us to leverage the dataset to explore predictors of behavior change, thereby improving the development of future treatments. Examining differences by race/ethnicity and other sociocultural characteristics will allow us to examine whether racial/ethnic disparities are reduced, which is a research priority of the Institute of Medicine [92].

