### Phase 3 analysis plan

We will use multilevel logistic regression to analyze the relationship between the measured predictors (gender, age, acculturation, alcohol situational norms) and recidivism (alcohol-related violations). Based on 2013’s DUI recidivism data in California [2], about 6 % of individuals with a DUI arrest experienced a subsequent crash or violation that was alcohol-related within 12 months. Thus, we acknowledge that we may not have the power to detect differences without a large sample size (e.g., 1500/group). We will instead examine whether predictors of heavy drinking (gender, race/ethnicity, age, acculturation, alcohol situational norms) are predictive of recidivism (i.e., alcohol-related violations). We choose predictors of heavy drinking because there is a lack of research examining predictors of recidivism among Latinos. These findings will assist with the development and refinement of future treatments in this population. The rare nature of alcohol-related violations and crashes [2] means that sparse data may cause estimation problems due to separation issues and our models may be limited. Given the limitations on the models that can be analyzed, we recognize this aim is exploratory and that a power analysis is at risk of providing excess confidence in our analysis.

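### The article promises to show who benefits most from CBT and whether ethnic disparities shrink, but the analyses it describes only relate characteristics to outcomes

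*Protocol article*

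**What the plan says.** Two sentences in the protocol article set questions about differential benefit.

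- Phase 2 procedures: "We will also examine predictors of CBT efficacy to further understand the characteristics of participants who benefit most from treatment". The same paragraph frames efficacy as CBT compared with usual care.
- Phase 3 Procedures: examining differences by race/ethnicity and other sociocultural characteristics "will allow us to examine whether racial/ethnic disparities are reduced".

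The analyses offered to answer them are worded as follows.

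- Specific aims, Aim 2: "examining whether race/ethnicity, gender, acculturation, and alcohol situational norms predict treatment outcomes and DUI recidivism".
- Overview of study procedures: "We will also analyze predictors of treatment response and recidivism by examining whether race/ethnicity, gender, acculturation, and alcohol situational norms predict treatment outcomes".
- Phase 3 Procedures, drinking outcomes: "we will explore whether gender, race/ethnicity, acculturation, and alcohol situational norms are predictors of our primary treatment outcomes".
- Phase 3 analysis plan, recidivism: "We will use multilevel logistic regression to analyze the relationship between the measured predictors (gender, age, acculturation, alcohol situational norms) and recidivism". After conceding low power for detecting differences, it continues: "We will instead examine whether predictors of heavy drinking (gender, race/ethnicity, age, acculturation, alcohol situational norms) are predictive of recidivism".

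In the Phase 2 analysis plan, age, gender and ethnicity appear only as characteristics to be controlled for in the arm comparison.

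**The concern.** Who gains most from CBT, and whether CBT narrows an ethnic gap, are both questions of effect modification: does the difference between CBT and usual care change with the characteristic? A regression of outcome on characteristics answers another question, namely who drinks less or reoffends less whichever programme they attended. The Overview makes the substitution explicit, since it says treatment response will be studied by looking at whether characteristics predict outcomes.

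Followed as written, the plan could report a prognostic factor as a predictor of CBT efficacy. It could also pass over a characteristic that truly changes the CBT effect. Either error would carry into the refinement of future treatments, which is the use the article intends for these results.

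A smaller inconsistency sits alongside. The first predictor list in the Phase 3 analysis plan omits race/ethnicity. The second list in that section includes it, as do Aim 2, the Overview and Phase 3 Procedures.

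**Working it through.** **No figure to reproduce.** The article gives no effect size, SD, alpha or power for these analyses. Its one sample-size remark (1500 per group) concerns detecting differences in recidivism and does not bear on this point.

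**Inputs from the article.** 300 participants randomised 1:1 and 85% retained at 6 months (Flow rates), so 0.85 × 300 = 255 analysed. Expected shares are 50% Latino, 65% male and 10% African American (Participants).

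**Assumed for illustration.** Outcome SD 1, two-sided 0.05, 80% power, no clustering and no precision gain from covariates.

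**Step 1: what a predictor coefficient measures.** Let *b* be the gap between two groups under usual care and *i* the difference in CBT effect between them. The gap is then *b* under usual care and *b + i* under CBT. With 1:1 allocation, a model with no interaction estimates their average, *b + i/2*. That one number cannot show whether the gap differs between arms.

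**Step 2: a prognostic factor read as a modifier.** For a 50/50 predictor:

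- SE(main effect) = 2/√255 = 0.125.
- With *b* = 0.35 and *i* = 0, power = Φ(0.35/0.125 − 1.96) = Φ(0.84) ≈ 0.80.

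A factor with no bearing on CBT benefit is therefore significant about 80% of the time. The 0.35 is illustrative: it equals 2.80 × 0.125, so the 80% follows by construction.

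**Step 3: simulation.** 2,000 trials of 255, a 50% subgroup, and linear models with arm and predictor, with and without the interaction.

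| Case | *b* | *i* | *b + i/2* | Main-effect model significant | Interaction significant |
|---|---|---|---|---|---|
| A, prognostic only | 0.4 | 0 | 0.4 | 89% | 6% |
| B, modifier only | 0 | 0.8 | 0.4 | 88% | 88% |
| C, modifier offset by a usual-care gap | −0.4 | 0.8 | 0 | 5% | 89% |

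Without the interaction, A and B look the same, although the gap is 0.4 in both arms in A and goes from 0 to 0.8 in B. In C a large difference in benefit disappears. The interaction term separates all three.

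**Step 4: what the interaction could detect.** SE(interaction) = 0.125/√(f(1 − f)), where f is the subgroup share. The detectable difference is 2.80 × SE.

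- 50/50 (Latino): SE = 0.125/0.5 = 0.25, detectable 0.70 SD.
- 65/35 (gender): SE = 0.125/√0.2275 = 0.263, detectable 0.74 SD.
- 10/90 (African American): SE = 0.125/0.3 = 0.417, detectable 1.17 SD.

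For a 50/50 predictor, an interaction of 0.35 SD has power Φ(0.35/0.25 − 1.96) = Φ(−0.56) ≈ 29%.

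**The case against.** The strongest reply is that silence is not a specification. This is a condensed article, it gives no equation, and it nowhere excludes arm or says the arms will be pooled. For the drinking outcomes Phase 3 states only a question, and the phrases about CBT efficacy and treatment response would suit a moderation analysis. A fuller plan might contain the interaction. This stands to the extent that the absence is inferred for those outcomes; a reader might conclude that the models contain main effects only, and the document does not establish that. What survives is narrower: the article says how the questions will be answered and draws an inference about disparities from it, and that inference does not follow from the analyses described. Those sentences would need correcting whatever a fuller plan says.

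Second, the recidivism model is a reasoned and disclosed choice, given about 6% events in 12 months and the separation problems the article anticipates. That is accepted. An interaction is not asked for there, only a prognostic label.

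Third, Phase 3 is already called exploratory. This limits the consequences, but does not make a prognostic analysis estimate effect modification.

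Two further readings go too far. A reader might infer that a benefit which reverses between groups would nearly always go unseen. The 5% in case C requires a usual-care gap that exactly cancels half the interaction; without that gap (case B) the predictor is flagged about 88% of the time, though still not as a modifier. A reader might also infer that disparity reduction in this sense is the reason for the trial. The article's stated reasons are DUI recidivism and poor access to alcohol treatment among Latinos, and it addresses access by delivering CBT inside the DUI programs.

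**Conclusion.** The point holds as a mismatch between stated questions and stated analyses. The promises in Phase 2 procedures and Phase 3 Procedures concern variation in the CBT effect, while Aim 2, the Overview and Phase 3 describe prediction of outcome. As described, the analyses cannot tell prognostic factors from modifiers. The size is illustrative: about 80% significance for a purely prognostic 0.35 SD factor, and possible loss of a real modifier when a usual-care gap offsets it. These figures rest on the assumed SD, alpha and independence. The Phase 2 analysis plan itself says rolling groups violate independence, so actual precision may differ. The primary arm comparison is not affected. The omission of race/ethnicity from one list is a separate editorial inconsistency and adds nothing to the argument about interactions.

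**What to change.** - For heavy drinking and percent days abstinent, state models with arm, predictor and arm-by-predictor terms for race/ethnicity, gender, acculturation and baseline situational norms. Table 2 also measures norms at both follow-ups, but those values come after randomisation and treatment may change them.
- Report the CBT effect with its 95% CI at each level of the characteristic, under the exploratory label Phase 3 already uses.
- Describe every model without the interaction, including the sparse recidivism model, as prognostic only.
- Wherever no interaction is fitted, reword the two promises in Phase 2 procedures and Phase 3 Procedures to speak of predictors of outcome.
- Reconcile the two predictor lists in the Phase 3 analysis plan so that both treat race/ethnicity the same way.

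The cost is an arm term and an interaction per model plus some wording; no new data are needed. The price is imprecision: under the assumptions above, only interactions of about 0.70 SD (50/50 predictor) or 0.74 SD (gender) reach 80% power. A non-significant interaction must not be read as evidence of equal benefit.

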**Fig. 1 Fig1:**

Intervention and data collection flow

#### CBT group counsellors and training

Counsellors in the DUI program are registered through state certification and have at least two years of experience in substance abuse counselling. We will use a training model that was used successfully in our previous implementation of CBT treatment [80]. DUI counsellors will be trained to deliver the CBT through a 2-day didactic training, followed by supervised practice in conducting the entire 9-session treatment (the training phase) with DUI program clients in the three DUI programs, followed by a 1-day didactic refresher training. Training will include three parts: (1) An introduction to the CBT model including theory of how thoughts, behaviors, and alcohol use interact; (2) A detailed review of each of the nine weekly sessions in the treatment manual followed by a counsellor role-play session, including feedback from trainers and group participants; and (3) A discussion of sensitive issues that may arise in the group (e.g., group management issues, such as how to balance the talking among participants, how to handle participants at different stages of change with their drinking, clinical issues such as intimate partner violence, and emergencies such as suicide ideation). Counsellors will participate in weekly, individual or group supervision meetings. Audio recordings will be reviewed during supervision meetings to support ongoing adherence and to highlight areas for improvement.

#### CBT group fidelity and adherence monitoring

We will use methods from our previous studies to assess the fidelity of CBT and adherence to session content [81]. We will randomly select 15 % of CBT session recordings to be coded by trained CBT coders. Two individuals with Masters Degrees in either psychology or public health/nursing will be recruited to code. They will receive 24 h of training (covering the nine CBT sessions). Coder training will review treatment materials, key points of the sessions, and guidelines of the rating form, which will be adapted from the Yale Adherence and Competence Scale (YACS; [82]). The YACS [82–85] has been utilized in large clinical trials such as Project MATCH [83, 84]. Coders rate therapist adherence and competence in delivering manualized treatments for alcohol and other drug use related problems [82, 86]. We will estimate interrater reliability using the intraclass correlation coefficient (ICC [87]). The fidelity measure will allow us to describe counsellors’ fidelity to CBT and adherence to the treatment, and whether the counsellors are competent in delivering the CBT. We anticipate that counsellors will demonstrate high fidelity prior to the start of the efficacy trial, and that there will be little variability during implementation due to ongoing supervision [81]. Therefore, we do not evaluate the relationship between fidelity and outcomes (Table 2).

**Table 2 Tab2:** Data collection measures

Measure	Instrument	Baseline	3 months	6 months
Alcohol use: days abstinent, heavy drinking; typical quantity, frequency^a^	DDQ	X	X	X
Alcohol-related self-efficacy^b^	AASE	X	X	X
Intent to drink and drive^b^	BADDS	X	X	X
Alcohol-related negative consequences^b^	SIP-AD	X	X	X
Alcohol-related health consequences (i.e., injuries, hospitalizations)^b^	NSDUH	X	X	X
Attitudes about drinking and driving^b^	BADDS	X	X	X
Demographic information^c^	Sociodemographic form	X		
Acculturation^c^	PAS-3	X		
Alcohol situational norms^c^	ASN	X	X	X

*DDQ* Daily Drinking Questionnaire, *AASE* Alcohol Abstinence Self-Efficacy Scale, *BADDS* Behaviors and Attitudes Drinking and Driving Scale, *NSDUH* National Survey on Drug Use and Health (NSDUH), *SIP*-*AD* Short Inventory of Problems Alcohol and Drugs (adapted for alcohol only in this study), *PAS*-*3* Proxy Acculturation Scale, *ASN* alcohol situational norms

^a^Primary outcome

^b^Secondary outcome

^c^Covariate

